## **Abstract (plain language summary)**

**Title:** Reducing the frequency of follow up and task sharing in the treatment of uncomplicated severe acute malnutrition: an evaluation of monthly visits and home-based surveillance for access-limited and high-burden settings

**Research design:** This study will be conducted as a stratified cluster randomized trial. The unit of randomization will be the outpatient therapeutic feeding center. The 10 health centers will be stratified by size, and centers within a stratum will be randomized in a 1:1 ratio to one of two schedules of treatment: (1) standard weekly visits or (2) monthly visits with support for home-based surveillance.

**Methodology:** Distribution of the therapeutic feeding rations, as well as medical and anthropometric surveillance of children being treated for uncomplicated severe acute malnutrition, will take place on a weekly or monthly basis until discharge according to the random assignment of the site. Caregivers in the monthly visit group will receive additional instruction at admission regarding home-based surveillance.

Routine program data on the child's anthropometric and clinical status at scheduled follow-up visits will be collected on standardized case report forms. All children will receive additional visits within the first two weeks of treatment and 3 months post-discharge to assess the child's anthropometric status.

### **Principal intervention:**

- (1) standard weekly follow-up during treatment for uncomplicated severe acute malnutrition
- (2) monthly follow-up with support for home-based surveillance

Regardless of intervention assignment, all children with uncomplicated severe acute malnutrition will receive standard medical care as per national guidelines.

### **Outcome variables:**

- Nutritional recovery, defined by being free from medical complications, MUAC  $\geq$  125 mm, and no edema for 2 weeks if admitted with edema.
- Hospitalization, defined as referral to inpatient care for weight/edema changes; failed appetite test; or clinical complication necessitating inpatient care.
- Weight gain (g / kg / day), defined as the difference in weight (g) from admission to week 4, to week 8 and to discharge divided by weight on admission (kg) and number of days between admission and week 4/week8/discharge among recovered children.
- Defaulting, defined as 3 missed scheduled facility visits in the weekly follow-up group and 1 missed scheduled facility visit in the monthly follow-up group.
- Relapse, defined as maternal report of admission to any therapeutic feeding program within 3 months of discharge from the index admission.

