## 2.0 STUDY OBJECTIVES AND ENDPOINTS

The study aims to strengthen the evidence base for more flexible ways to deliver nutritional treatment in humanitarian crises.

Primary objective:

To estimate the effectiveness of monthly vs. standard weekly follow up in the treatment of uncomplicated severe acute malnutrition in children aged 6 to 59 months in terms of nutritional recovery.

Secondary objectives:

- To estimate the effectiveness of monthly vs. standard weekly follow up in the treatment of uncomplicated severe acute malnutrition in children aged 6 to 59 months in terms of hospitalization.
- To estimate the effectiveness of monthly vs. standard weekly follow up in the treatment of uncomplicated severe acute malnutrition in children aged 6 to 59 months in terms of weight gain among recovered children.
- To estimate the effect of monthly vs. standard weekly follow up in the treatment of uncomplicated severe acute malnutrition in children aged 6 to 59 months in terms of the risk of defaulting.
- To estimate the effectiveness of monthly vs. standard weekly follow up in the treatment of uncomplicated severe acute malnutrition in children aged 6 to 59 months in terms of the risk of relapse within 3 months following discharge.
- To estimate program coverage in areas receiving monthly vs. standard weekly follow up in the treatment of uncomplicated severe acute malnutrition in children aged 6 to 59.
- To assess the cost-effectiveness of monthly vs. standard weekly follow up in the treatment of uncomplicated severe acute malnutrition in children aged 6 to 59 months in terms of cost per child treated and per child recovered.

Primary endpoint:

The primary endpoint is nutritional recovery, defined by being free from medical complications, MUAC  $\geq$  125 mm, and no edema for 2 weeks if admitted with edema.

Secondary endpoints:

- Hospitalization, defined as referral to inpatient care for :

- weight/edema changes: weight loss over 3 weeks; static weight over 4 weeks; onset of edema when previously absent; persistent edema 3 weeks following admission
  - failed appetite test
  - clinical complication necessitating inpatient care: fever, hypothermia, severe dehydration, repeated vomiting, severe respiratory distress, chest in-drawing, severe pallor with respiratory distress, malaria with signs of severity, abscess or extended skin lesions, very weak, apathy or unconscious, or convulsions

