#### 3.3. Study sites

Study activities will take place in 10 outpatient therapeutic feeding centers supported by UNICEF. The 10 outpatient therapeutic feeding centers will be staffed by research nurses trained to seek written informed consent and support data collection during all enrollment and follow-up visits. Children transferred for inpatient care will be followed by a research nurse until hospital discharge. Once medical complications are resolved, appetite has returned and/or edema is reduced, the child will resume treatment at the original outpatient therapeutic feeding center and study follow-up until program discharge.

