#### 4.6 Follow-up visits

At sites assigned to standard weekly follow up, follow up visits at the study sites will be scheduled every week until discharge from the nutrition program for a maximum of 12 weeks. At sites assigned to the monthly follow up, follow up visits at the study sites will be scheduled at 4, 8, 10 and 12 weeks until discharge from the nutritional program. At all follow up visits, program staff will measure appetite, weight, height/length (discharge only), MUAC, edema and conduct a clinical examination.

The child will be referred to the inpatient center during follow-up for weight/edema changes (weight loss over 3 weeks; static weight over 4 weeks; onset of edema when previously absent; persistent edema 3 weeks following admission); failed appetite test; or clinical complication necessitating inpatient care (fever, hypothermia, severe dehydration, repeated vomiting, severe respiratory distress, chest in-drawing, severe pallor with respiratory distress, malaria with signs of severity, abscess or extended skin lesions, very weak, apathy or unconscious, or convulsions). A child admitted for inpatient care will be followed on a daily basis at the hospital while receiving inpatient treatment. After stabilization, the child will resume outpatient management and study follow-up at his/her assigned outpatient facility. If the child's outpatient site was assigned to the monthly follow-up group, the child referred from inpatient care will be asked to return to the study site for outpatient management at 1, 4, 8, 10 and 12 weeks until discharge.

All caregivers will be instructed to return to the health center between scheduled visits if any clinical sign of concern develops at home. Spontaneous visits to a study health facility will be recorded with determination of the reason and treatment(s) provided.

At all follow-up visits, to understand utilization of the nutritional supplements in the household, all care givers will be asked to report average daily use of the supplement and return all finished and unfinished product.

At the discharge visit, caregivers knowledge, attitudes and practices related to the key danger signs and MUAC assessment for home-based surveillance will be assessed by standardized questionnaire (see Annex 9.2) in both the weekly and monthly follow-up groups. Compensation (e.g. 2 pieces of soap) for participation in the study will be provided to caregivers at the end of the discharge visit.

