## 7.0 ADMINISTRATIVE AND LOGISTICAL CONSIDERATIONS

### 7.1 Human resources

Each site will have a study team comprised of 2 study nurses, who will help take informed consent, collect background information at admission, and support high quality data collection at all enrollment and follow up visits, and 1 nutritional assistant who will support anthropometric assessment and data collection at all enrollment and follow up visits. There will be an additional study nurse assigned to the inpatient center, as well as 2 nurse supervisors to oversee activities at 5 sites each. Community health workers will conduct tracing of patients who do not attend regularly scheduled follow up and complete the unannounced safety visits, and issue reminders for the post-discharge follow-up visits. Four data entry clerks, under the supervision of a data manager, will conduct continuous double-data entry, comparison and cleaning. Members of the study team will be recruited locally for the duration of the study (approximately 19 months).

All locally recruited staff will be under the direct supervision of the Field Investigator, a trained medical doctor with experience in epidemiological research. The Field Investigator, recruited by Epicentre, will be responsible for the training and supervision of study staff and for coordination of all logistics and data collection activities in accordance with the study protocol and standard operating procedures.

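### Hospitalization is scored by referral from the outpatient site, so admissions that bypass the site are missed, and contact with the site differs by arm

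*Protocol*

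**What the plan says.** The Abstract (Outcome variables) gives the definition as "Hospitalization, defined as referral to inpatient care for weight/edema changes; failed appetite test; or clinical complication necessitating inpatient care". Section 2.0 repeats it in the formal endpoint list, opening with "Hospitalization, defined as referral to inpatient care for" and then listing the same three groups of reasons. It is therefore not a shortening confined to the abstract. Section 3.9 compares the proportion hospitalized between arms.

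Section 4.6 describes referral as something that happens in outpatient follow-up, for those same reasons: "The child will be referred to the inpatient center during follow-up for weight/edema changes". It then describes admission separately: "A child admitted for inpatient care will be followed on a daily basis at the hospital while receiving inpatient treatment". Section 3.3 adds: "Children transferred for inpatient care will be followed by a research nurse until hospital discharge". Section 7.1 provides the staff: "There will be an additional study nurse assigned to the inpatient center". Section 4.4 gives each enrolled child a bracelet and card bearing the study number, partly for use on transfer to hospital.

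For unscheduled contact, Section 4.6 says: "Spontaneous visits to a study health facility will be recorded with determination of the reason and treatment(s) provided". The protocol does not say how to score an enrolled child who is admitted without a site referral, or a referral that is not completed. The text on direct inpatient admission in Sections 4.4 and 5.3 concerns children not yet enrolled.

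**The concern.** The endpoint's name suggests an inpatient stay, but its definition counts a decision made at the outpatient site. The two part company in two situations:

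- An enrolled child falls ill between visits and is carried straight to hospital. There is an admission but no site referral, so the child is not counted.
- A child is referred and the caregiver does not go. There is no admission, but the child is counted.

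The first matters more for the comparison. A site can refer only a child it sees, and how often it sees the child is what the trial randomizes. An outcome whose detection depends on the randomized exposure can show a difference that reflects detection alone.

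Death is not among the endpoints listed in Section 2.0, so hospitalization is the listed endpoint closest to serious deterioration during treatment. It will be read as evidence on safety, which Section 1.1 says must be clear before a reduced schedule is adopted.

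**Working it through.** **Contacts at which a referral can arise (Section 4.6).** In the weekly arm, "follow up visits at the study sites will be scheduled every week until discharge from the nutrition program for a maximum of 12 weeks", so up to 12. In the monthly arm, visits fall at weeks 4, 8, 10 and 12, so up to 4, with one more at week 1 for children coming from inpatient care. Both arms also have one unannounced home visit in the first two weeks (Section 4.7), and spontaneous visits at any time.

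**How the literal definition scores each case.**

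| Enrolled child | Admitted? | Counted? |
|---|---|---|
| Referred by the site, admitted | yes | yes |
| Returns to the site between visits, is referred, admitted | yes | yes |
| Referred by the site, does not go | no | yes |
| Taken directly to inpatient care | yes | no |

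**Formula.** The protocol gives no figure for this endpoint, so there is nothing to reproduce and every input below is an assumption. Let h be the true admission risk, b the share of admissions that bypass the site, and f the share of referrals not followed by admission. Admissions through the site are h(1 - b). Referrals issued are that quantity divided by (1 - f). So:

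scored risk = h(1 - b)/(1 - f)

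**Ratio with equal h and equal f in both arms.** Both cancel, leaving (1 - b monthly)/(1 - b weekly).

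| b weekly | b monthly | Ratio |
|---|---|---|
| 5% | 15% | 0.85/0.95 = 0.89 |
| 5% | 30% | 0.70/0.95 = 0.74 |
| 10% | 15% | 0.85/0.90 = 0.94 |
| 10% | 30% | 0.70/0.90 = 0.78 |
| equal in both arms | | 1.00 |

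The range is 0.74 to 0.94 if bypass differs as assumed, and exactly 1.00 if it does not.

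**Absolute scale, with f = 10% in both arms and b = 5% weekly.**

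- h = 10%: weekly 0.10 x 0.95/0.90 = 10.6%. Monthly is 0.10 x 0.85/0.90 = 9.4% at b = 15% and 0.10 x 0.70/0.90 = 7.8% at b = 30%. The spurious difference is -1.1 to -2.8 points.
- h = 5%: weekly 5.3%, monthly 4.7% to 3.9%. The spurious difference is -0.6 to -1.4 points.

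**Referrals not taken up.** At f = 10% to 20% the count rises by a factor of 1/0.90 = 1.11 to 1/0.80 = 1.25. If f is the same in both arms, the ratio does not move. If f is 10% weekly and 20% monthly, the ratios above are multiplied by 0.90/0.80 = 1.125; in the reverse case, by 0.80/0.90 = 0.89. Unequal uptake can therefore push the ratio either way.

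**The case against.** **The protocol sends sick children through the site.** Caregivers in both arms are told to return to the health center if a sign of concern appears (Sections 3.5, 4.6, 5.2), and those in the monthly arm get extra training on danger signs. A child who does return and is then referred is counted. This stands, and it limits the problem to children who bypass the site. The protocol neither describes nor quantifies that group.

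**Admission may be what was meant.** Much the same list of presenting conditions leads to referral in Section 3.4 and to direct admission in Section 4.10, so the terms are used loosely. The case report forms and any SAP might settle the scoring. That is possible, but both places that define the endpoint say referral, and nothing in the protocol overrides them.

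**Stronger readings that a reader might infer, and that the documents do not support:**

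- *That monthly follow-up will look safer than it is.* This needs higher bypass in the monthly arm, and the documents give no rate for either arm.
- *That counting a declined referral is an error.* It is a defensible choice: referral records deterioration judged to need inpatient care, whether or not the family can travel. The name fits poorly, but the measure is a reasonable one.
- *That the endpoint contradicts the costing in Section 3.10.* Costing inpatient care does not require the same count as a clinical endpoint.
- *That these events are lost to the trial.* Section 5.9 requires all adverse events to be reported within 24 hours, and Section 4.8 traces missed visits. The gap is in the endpoint that is compared between arms.

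**Conclusion.** The point holds in a limited form. As written, the endpoint omits inpatient admissions that did not pass through the outpatient site, and it includes referrals that led to no admission. Because scheduled contact with the site differs by arm, a difference between arms could arise without any difference in admissions.

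The ratio of 0.74-0.94 rests wholly on assumed bypass of 5-10% (weekly) and 15-30% (monthly), equal true risk and equal referral uptake. It shows what the definition would allow; it is not a prediction. The definition needs correcting whatever the true rates are, because the data as scored could not tell a real difference in admissions from a difference in route. It concerns one secondary endpoint.

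**What to change.** Reword the endpoint in the Abstract and Section 2.0. Hospitalization should be any inpatient admission of an enrolled child during treatment, by any route, ascertained in the same way in both arms from the inpatient study nurse's record and matched on the study number from the bracelet or card. Report two further quantities by arm as descriptive outcomes: referrals issued, and referrals not taken up. This keeps the information that the present definition captures.

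Admissions learned of only through missed-visit tracing should be reported separately and kept out of the main count. Tracing is triggered by missed scheduled visits, and the number of those that can be missed also differs by arm.

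The inpatient nurse and the identification system are already planned. The cost is the wording and some added record matching. One weakness remains: admissions outside the study's inpatient center may still be missed, and the report should say so. No clinical rule changes.

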## 1.0 BACKGROUND AND RATIONALE

### 1.1 Management of severe acute malnutrition

Severe acute malnutrition (SAM) affects at least 19 million children worldwide, and through its detrimental effects on immune function, contributes to high child morbidity and mortality. Historically, the treatment of children with SAM included the systematic hospitalization of all cases and inpatient nutritional rehabilitation with milk-based diets over 3-4 weeks. In 2007, a joint United Nations statement endorsed a new model for the management of SAM that combines outpatient treatment with ready-to-use therapeutic foods (RUTF) for uncomplicated cases and inpatient treatment only for complicated cases. In this model, 80 to 90% of children with uncomplicated SAM are treated on a weekly outpatient basis, where they receive rapid health assessment and weight check by a nurse, a physical exam if signs of illness or weight loss are present, and a therapeutic ration of RUTF for home use. The shift from systematic inpatient to outpatient-based care has decreased the need for highly trained medical staff and inpatient bed capacity, reduced the risk of cross-infection among ill children, and importantly eliminated the burden on caregivers and children spending several weeks in hospital. Although outpatient care places increased responsibility on caregivers to supervise administration of RUTF at home and monitor the child's clinical condition between weekly visits, low mortality rates (e.g. 1 to 5 %) have been achieved.

While the outpatient treatment model represents great progress in the management of SAM, the current model remains impractical in some contexts, particularly in settings where geography (e.g. the south of Chad), security (e.g. Somalia) or nomadic livelihoods (e.g. Kenya) make frequent movements to a health facility difficult or impossible. In settings with a high incidence of acute malnutrition (e.g. Niger and Northeastern Nigeria), such frequent visits may also overwhelm public health capacity, resulting in reduced coverage of treatment. Therefore, in many settings, it may be necessary to identify an alternative delivery model for the outpatient management of uncomplicated SAM.

While there is some operational experience with biweekly schedules of follow up, evidence for further reduced schedules in the outpatient treatment of SAM is extremely limited. To our knowledge, the only experience to date comes from the 2012 Médecins Sans Frontières (MSF)-France project in Yao, Chad, where an active screening and treatment program using mobile teams extended the standard, weekly schedule of follow up to a monthly schedule (personal communication, [name]). Unfortunately, flooding in the program area reduced access and forced the closing of treatment sites, limiting our understanding of the feasibility and effectiveness of this model.

If a reduced schedule of follow up, with caregiver support for home-based surveillance, is to be adopted where standard weekly follow up is not possible, there must be clear evidence that such strategies can be used safely and effectively while remaining acceptable to caregivers. A reduced, monthly schedule of follow up has the potential to reduce the opportunity cost of

caregivers seeking treatment, increase access to adequate care and support among vulnerable children, and allow for more efficient delivery in numerous contexts.

## 1.2 Study rationale

While it is estimated that at least 19 million children suffer from SAM each year, only 7-13% of these children received treatment in 2012. The challenges to increasing access to treatment are multiple, but reliance on a weekly schedule of follow up can limit operations to areas where access and frequent visits to a health facility are not possible. In contexts where weekly follow up is not feasible, humanitarian organizations may be forced to curtail or limit operations, resulting in fewer children receiving life-saving treatment and care and reducing the impact of nutritional programs in these settings.

To our knowledge, there has been no high quality research on the use of alternative schedules in the treatment of uncomplicated SAM among young children. Important research gaps in the evidence base therefore remain, including a lack of information on the feasibility, acceptability, safety and effectiveness of alternative delivery models. This study will apply the gold standard design for evaluation, with the aim to produce evidence of sufficient quality and rigor to fill the existing research gap and inform future programs. These results will be drawn from an on-going nutritional program, and therefore aim to be directly generalizable to other operational settings where the standard protocol may be impractical. This includes contexts with ongoing conflict or security constraints, as well as settings with difficult geographical access and a high incidence of acute malnutrition. The operational experience provided by this research will also be an opportunity to better understand the type of support (e.g. home visits to follow absences, increased support/training of caregivers) that would be necessary for a monthly schedule of follow up to be feasible and eventually applicable in other contexts.

## 1.3 Innovation and relevance for the community-based management of SAM

The outpatient management of SAM has been recommended by the World Health Organization, WFP, UN Standing Committee on Nutrition and UNICEF since 2007. However, reliance on a weekly schedule of follow up limits operations to areas where access and frequent visits to a health facility are possible and potentially reduces the number of children receiving treatment. In contexts where weekly follow up is not feasible (e.g. Chad where access was limited due to heavy rains; Somalia where access is reduced due to high insecurity), programs have been forced to curtail operations, resulting in fewer children receiving treatment. Similarly in contexts where the absolute number of children needing treatment is very high (e.g. northeastern Nigeria), the burden of the traditional schedule of follow up can limit coverage and reduce program impact. To our knowledge, no program has implemented a reduced schedule of follow up (beyond biweekly visits) and documented safety or efficacy. This proposal therefore represents innovation as this is the first time a strategic reduction in the schedule of follow up will be implemented and evaluated within the community-based treatment model.

This study is intended to provide programs with greater flexibility to consider more innovative models of treatment and to extend operations into areas previously unsuitable for treatment programs. If the results of this study can confirm that monthly visits in the treatment of uncomplicated SAM can achieve similar rates of nutritional recovery as standard weekly visits, programs will have the evidence needed to consider adopting a reduced schedule of follow up and provide treatment in a greater number of settings. Evidence provided by this study could support increased coverage in existing programs, as a reduced schedule of follow up in an existing program could decrease the program burden per child and allow for an increase in the proportion of children covered using the same or fewer resources. These results could also allow more flexible and innovative programming in new settings where the standard protocol has been impractical, including contexts with nomadic populations, difficult geographical access, conflict or high incidence of malnutrition.

